## Abstract

**Background:**

Semivolatile organic compounds (SVOCs) comprise several different chemical families used mainly as additives in many everyday products. SVOCs can be released into the air as aerosols and deposit on particulate matter during use by dispersion, evaporation, or abrasion. Phthalates are SVOCs of growing concern due to their endocrine-disrupting effects. Human data on the absorption, distribution, metabolism, and excretion (ADME) of these compounds upon inhalation are almost nonexistent.

**Objective:**

The goal of this study is to develop a method for repeated inhalation exposures to SVOCs to characterize their ADME in humans.

**Methods:**

We will use diethylhexyl phthalate (DEHP), a major indoor air pollutant, as a model SVOC in this novel protocol. The Swiss official Commission on Ethics in Human Research, Canton de Vaud, approved the study on October 14, 2020 (project-ID 2020-01095). Participants (n=10) will be repeatedly exposed (2 short daily exposures over 4 days) to isotope-labeled DEHP (DEHP-d4) to distinguish administered exposures from background exposures. DEHP-d4 aerosols will be generated with a small, portable, aerosol-generating device. Participants will inhale DEHP-d4-containing aerosols themselves with this device at home. Air concentrations of the airborne phthalates will be less than or equal to their occupational exposure limit (OEL). DEHP-d4 and its metabolites will be quantified in urine and blood before, during, and after exposure.

**Results:**

Our developed device can generate DEHP-d4 aerosols with diameters of 2.5 μm or smaller and a mean DEHP-d4 mass of 1.4 (SD 0.2) μg per puff (n=6). As of May 2023, we have enrolled 5 participants.

**Conclusions:**

The portable device can be used to generate phthalate aerosols for repeated exposure in human studies.

**International Registered Report Identifier (IRRID):**

DERR1-10.2196/51020

## Introduction

The general population is exposed every day to semivolatile organic compounds (SVOCs) through inhalation [1-4], but few data exist on the internal (eg, blood) concentrations of these compounds when inhaled. One reason for this lack of data is the absence of a device to aerosolize SVOCs for controlled human exposure over several days. These compounds cannot be tested in common devices used for volatile chemicals such as solvents in whole-body exposure chambers. SVOCs are found in the air as liquid aerosols and deposited onto solid particles that are easily resuspended in the air and directly available through inhalation [5]. They are used as active ingredients in pesticides, cleaning agents, and personal care products, as well as additives in materials such as plastics, floor coverings, furnishings, and electronic components [4]. More than a thousand SVOCs are high-production-volume chemicals (HPVCs) [6]. Many of these have been associated with adverse health effects and have since been removed from commercial use [7,8]. Some are presumed (category 1B) endocrine-disrupting chemicals (EDCs) [9,10], including, among others, phthalates [11-14], brominated flame retardants [15], bisphenol A [16], nonylphenol [17], and some pesticides [18]. SVOCs are found in higher abundance indoors than outdoors [19,20] and are detected in both blood and urine collected from the general population [21]. This confirms the omnipresent and concurrent body burden.

Phthalates are a specific family of SVOCs used to impart flexibility to polymer plastics (ie, plasticizers) [22]. Phthalates are not covalently bound to the polymer matrix. Therefore, they can migrate to the surface and be slowly released into the air [21-24]. Phthalates with short alkyl chains, such as diethyl phthalate (DEP), have the highest vapor pressures and can also be released in the air in the vapor phase. Phthalates with long alkyl chains, such as diethylhexyl phthalate (DEHP), have lower vapor pressures and tend to adsorb to aerosol particles or dust [23] (Figure 1). DEHP has been reported to be the most abundant phthalate in house dust, with measured concentrations up to 5.3 mg/g [24,25].

Children and adults living in industrialized countries are estimated to spend around 17-19 hours and 21 hours per day indoors (ie, at home and in the working environment), respectively [26]. There is considerable concern regarding phthalate exposures because several epidemiological studies have shown associations between exposures to some phthalates and retarded male reproductive development [11,12], altered semen quality [13,14], endometriosis [27,28], and respiratory diseases in children [29]. When inhaled, phthalates can reach the alveoli, be absorbed into the blood, and then be distributed to potential target tissues, where they may trigger an effect. Therefore, absorption rates (ie, rate at which the molecule enters blood), internal doses (ie, parent compound concentrations in blood), as well as metabolic and elimination rates (ie, rate of metabolites’ formation and elimination, usually in urine), are important toxicokinetic parameters to accurately determine the total exposures in the human body and, thus, potential risks to the population. Although urinary metabolite ratios were reported to be different between humans and animals [30-34], these toxicokinetic parameters have not been studied in humans exposed to phthalates through inhalation as a single exposure route. The few human toxicokinetic studies conducted with phthalates were mainly after ingestion [35-38]. A total of 2 human studies have been conducted on phthalates, including simultaneous exposure through the skin and inhalation routes [39,40]. These studies only provided estimated toxicokinetics (absorption, distribution, metabolism, and excretion [ADME]) for the inhalation route. Since inhalation is considered a significant indoor route of exposure for some phthalates [41], toxicological studies need to be performed to understand phthalates’ ADME through this exposure route. However, a procedure to expose healthy participants to SVOCs is lacking due to the absence of devices for human studies with SVOCs through inhalation. We aim to fill these gaps by describing the required steps to obtain human ADME data after inhalation. The SVOC selected in this study is DEHP, a model SVOC due to its major presence in the indoor environment (air and dust) and human populations (urine). This study is divided into 2 parts. Part I describes the dosing procedure and how to generate aerosols at environmentally relevant phthalate concentrations with a device suitable for chronic inhalation exposure. Airborne phthalate aerosols will be produced based on the technology of commercially available “electronic nicotine delivery systems” (ENDS), which have proven efficacy in generating aerosols for human use [42,43]. ENDS are generally used to generate nicotine or flavored aerosols from highly viscous liquids such as glycerol (viscosity=1412 mPa·seconds) making this technology suitable for viscous chemicals such as some phthalates. Part II provides the study protocol for participants exposed to ring-deuterated DEHP for several days. Unisanté has strong expertise in toxicological studies with healthy participants and has adapted its protocols for repeated, at-home exposure. We will show the results of the first participant here as proof of concept.

**Figure 1 figure1:**
[figure not shown]
Generic chemical structure of phthalates, where R and R’ are alkyl or aryl moieties (left), and chemical structure of diethylhexyl phthalate (DEHP) (right).

## Methods

### Part I: Dosing Protocol

#### Portable Dosing Device

The commercial ENDS “Endura T20-S” (Innokin) was chosen as the portable dosing device for participants’ exposure to DEHP. ENDS consists of a battery-powered heated coil that functions as a thermal atomizer, a mouthpiece, and an e-liquid tank. Generally, the e-liquid is mainly composed of nicotine, flavoring agents, and ethanol in a base of propylene glycol (PG) and vegetable glycerol (VG). Base composition can vary from a PG/VG ratio of 20/80 to 70/30 and is typically 50/50. When the user activates the heated coil by pressing a button on the ENDS, the e-liquid is vaporized, releasing a flavored nicotine-containing aerosol called a “puff.” The user inhales this aerosol through the mouthpiece.

#### E-Liquids

Aerosols generated by ENDS are complex mixtures containing volatile and semivolatile gases (mainly PG and glycerol) and nonvolatile particles (mainly glycerol, PG, and nicotine) [44,45]. The e-liquid formulated in this study is composed of glycerol (purity 99.5%, Hänseler Swiss Pharma), PG (PG 0 mg/mL nicotine, Revolute), ethanol (absolute for analysis EMSURE, Supelco, Merck), and DEHP. Ring-deuterated DEHP (DEHP-d4, CAS# 93951-87-2, Sigma Aldrich) is used to differentiate exposures generated in our experiment to environmental and laboratory DEHP contaminations.

#### Aerosol Generation and Vaping Machine

To adapt the ENDS to generate DEHP aerosols at controlled concentrations, we used a vaping machine that was developed in the Unisanté laboratory in collaboration with the University Centre of Legal Medicine of Lausanne (CURML) [46]. The purpose of the vaping machine was to replicate the puffing behavior of an individual using an ENDS according to the method n°81 recommended by the Cooperation Centre for Scientific Research Relative to Tobacco (CORESTA) [47]. This method describes the requirements for the generation and collection of e-cigarette aerosols for analytical testing purposes and led to an ISO (International Organization for Standardization) standard (20768:2018). Our vaping machine included 3 ports, each for an ENDS head (e-liquid tank, atomizer, and mouthpiece), a power supply, a piston syringe, a pinch-valve system, and silicon tubing (Figure 2). The machine was equipped with its own power supply, which replaced the individual ENDS batteries. This provided a steady-state power of 12 W throughout all experiments. The replacement of the ENDS battery by the machine’s power supply precisely controlled puff duration during the experiments. The piston, in combination with the pinch valve system, controlled the puff volume, that is, the volume leaving the ENDS. Puff volumes were trapped by n-hexane in subsequent glass impingers (with P1 porosity fritted nozzle tip, joint connection NS 29/32, Bistabil, Sigma Aldrich) for analytical analysis. Puff duration (3 seconds per puff), volume (55 mL per puff), and frequency (30 second between puffs) were set up as per CORESTA criteria. Tests were carried out in triplicates. Control tests served to verify that the entire setup was not contaminated by DEHP-d4. A total of 3 ENDS with 0.8-ohm atomizers were used for all the experiments. New atomizers were used in each experiment.

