#### Participant Exposure

Participants will use the portable aerosol-forming device themselves, first in our facilities (day 1) and then at home (days 1-4). The e-liquid will have a PG/VG ratio of 50/50 with 1% (w/w) ethanol and 0.02% (w/w) DEHP-d4. The participants enrolled in the study will press a button on the ENDS battery. The coil will heat the e-liquid, generating an aerosol with DEHP concentrations less than or equal to the OEL.

The e-liquid will be prepared in advance for DEHP-d4 quantification analysis and will be stored at room temperature during the exposure week. A fraction of the e-liquid will be sent to the analytical laboratory of EPFL to confirm the DEHP-d4 concentration in the e-liquid, and the rest will be frozen at –20 °C until use. On the day of the first exposure to DEHP, the e-liquid will be defrosted. A vial with a weighted amount of e-liquid sufficient for 1-week exposure (ie, reserve) will be prepared for each participant. This vial will be stored at room temperature at the participant’s place, where they will use it to refill the ENDS e-liquid tank when needed. Therefore, a stability test is required to verify DEHP-d4 concentration after several days of storage at room temperature. This step is also important for the relevance of the study. On day 5, the participant will return the ENDS and the e-liquid vial, which will be weighed to calculate the exact amount of e-liquid puffed by the participant, hence the amount of puffed DEHP-d4.

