### Part II: Human Toxicological Study Protocol

As of May 2023, we have enrolled 5 participants. Following the whole protocol, participants will be able to generate aerosols with controlled DEHP concentrations using the ENDS and the prepared e-liquid at home for several days.

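### Mass per puff was measured only under machine conditions, so a controlled dose per puff or session at home is not shown, and the day-5 weighing cannot recover dose by session

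*Protocol article*

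**What the plan says.** **Bench.** Methods, Part I (Aerosol Generation and Vaping Machine) mounts only the ENDS heads. On power it says: "The machine was equipped with its own power supply, which replaced the individual ENDS batteries", and "This provided a steady-state power of 12 W throughout all experiments". It credits that replacement with the precise control of puff duration. The profile was fixed: "Puff duration (3 seconds per puff), volume (55 mL per puff), and frequency (30 second between puffs) were set up as per CORESTA criteria". On the atomizers: "New atomizers were used in each experiment". Results, Part I gives 36 puffs per experiment and a mean of 1.4 (SD 0.2) µg DEHP-d4 per puff (n=6). DEHP-d4 Exposure Concentration defines M_puff as this machine value and uses it for C_exp.

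**Home.** Under Participant Exposure, "The participants enrolled in the study will press a button on the ENDS battery", first in the facility and then at home through day 4. The Abstract gives two exposures a day over 4 days. Participants are instructed, and the first exposure is supervised (Participant Timeline). The ENDS and the vial are weighed on day 5 to obtain the amount puffed.

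**Claim.** Results, Part II states that "participants will be able to generate aerosols with controlled DEHP concentrations using the ENDS and the prepared e-liquid at home for several days". The Discussion likewise presents the method as giving controlled concentrations for controlled human exposure studies.

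**The concern.** Three things were held constant on the bench and are not shown to be constant at home: electrical power, puff length and draw, and the age of the atomizer. The bench mean and SD therefore describe the machine set-up, while the claim of control concerns self-operated use over several days.

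What is at stake is dose by session. The Statistical Analysis section estimates absorption and elimination rates for each participant and compares them by age and gender. The Discussion hopes to learn about accumulation under repeated exposure. If dose varies from session to session and only the 4-day total is known, that variation can be mistaken for a difference in absorption or for accumulation.

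**Working it through.** **1. Reproduce the article's figures.**
- Mass per puff = concentration × puff volume = 25.4 mg/m³ × 55 mL = 1.397 µg (stated 1.4).
- SD = 3.4 mg/m³ × 55 mL = 0.187 µg (stated 0.2). CV = 0.2/1.4 = 14%.
- Volume per experiment = 36 × 55 mL = 1.98 L (stated 2 dm³).

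All three agree. The bench arithmetic is not in question.

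**2. What the SD covers.** With n=6, the 95% prediction interval for one further bench value is 1.4 ± 2.571 × 0.2 × √(1 + 1/6) = 0.84 to 1.96 µg. Since 36 puffs were collected per experiment, each of the six values is probably an average over many puffs. The interval holds bench variation only: nothing in it reflects battery state, user behaviour or atomizer ageing.

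**3. Bench against home.**

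| Condition | Bench | Home |
|---|---|---|
| Power | Machine supply, steady 12 W | ENDS battery |
| Puff | Fixed: 3 s, 55 mL, every 30 s | Participant's button press and draw |
| Atomizer | New in each 36-puff experiment | Replacement not stated |
| Sessions | Single experiments | 2 per day × 4 days = 8 |

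Puffs per session are not stated in the text at hand. If one atomizer served all 8 sessions (an assumption), more than 36/8 = 4.5 puffs per session would take it past the number used in a bench experiment.

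**4. What the day-5 weighing can and cannot give.** It yields total e-liquid loss, and so one total dose D. The mean session dose is D/8. As an illustration with assumed figures, let session dose drift linearly from 0.75 to 1.25 of the mean over the 8 sessions. The total is still D, but the last session is 1.25/0.75 = 1.67 times the first. Metabolite levels would tend to rise for that reason alone. A 30-minute blood value divided by D/8 would be divided by 1/0.75 = 1.33 times the true first-session dose. Leaked liquid adds to D without being inhaled, and the Discussion reports leakage with the first participant.

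**5. Effect on the OEL statement.** The equation itself is not in the text at hand. From its listed terms, C_exp = M_puff × p / (V_tidal × IE). Take p = 2 per minute (the 30 s interval), V_tidal = 0.5 L, and IE = 12 to 20 per minute (assumed).
- IE = 12: 1.4 × 2 / (0.5 × 12) = 0.47 mg/m³.
- IE = 20: 1.4 × 2 / (0.5 × 20) = 0.28 mg/m³.
- At twice the puff mass: 0.93 and 0.56 mg/m³.

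To reach 2 mg/m³, mass per puff would have to rise 2/0.467 = 4.3-fold (IE 12) to 2/0.28 = 7.1-fold (IE 20).

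**6. A benchmark for checking real use.** At 0.02% w/w, 1.4 µg corresponds to 1.4/0.0002 = 7,000 µg = 7 mg of e-liquid per puff. If the 1.4 µg was not corrected for the 89% impinger recovery, the figure is 7/0.89 = 7.9 mg. Both assume that DEHP-d4 leaves in proportion to the liquid.

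**The case against.** The bench choice has a stated rationale: "The purpose of the vaping machine was to replicate the puffing behavior of an individual using an ENDS", following a CORESTA method that led to an ISO standard. New atomizers in each experiment are sound bench practice. Participants are trained, and their first session is watched. Above all, the individual total dose comes from weight and not from the machine value, which largely answers the worry about total dose differing between people. Atomizer changes and puffing instructions may be set out in the full protocol, which is not shown, and part of the Results between Table 1 and Figure 6 is not in the text at hand. All of this stands, and it narrows the point to dose by session. It does not close it: a standard puff profile does not show what these participants do, supervision is specified for one session, and a 4-day total cannot be split by session.

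A reader might go further in three ways that the document does not support:
- **That the bench dose fails to carry over.** No measurement on battery, with human puffs or with a used atomizer is reported, so neither the size nor the direction of any difference is known.
- **That the OEL statement is undermined.** As an average over breaths it keeps a several-fold margin under the assumed rates.
- **That the Abstract makes the same claim.** Its conclusion speaks of repeated exposure in human studies and does not mention controlled concentrations.

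**Conclusion.** The point holds in a limited form. The 1.4 (SD 0.2) µg per puff and its 14% CV are established for machine conditions only. The statements in Results, Part II and the Discussion that exposure is controlled go beyond that evidence. Total dose per participant is measured independently, apart from leakage. Dose by session is not, and the individual absorption estimates and any reading on accumulation depend on it.

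The size of the problem cannot be computed from the document. The 1.67-fold example shows only what an unchanged 4-day total could conceal; it is not an estimate. The conclusion assumes that the missing Results text holds no bridging test. The reassurance on the OEL assumes 2 puffs and 12 to 20 breaths per minute.

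**What to change.** 1. Weigh the ENDS immediately before and after the supervised day-1 exposure and record the number of puffs. Use that session dose with the 30-minute blood sample. Compare mass per puff with the bench-implied 7 mg (7.9 mg if the 1.4 µg is not recovery-corrected).
2. Optionally, run the complete ENDS on its own battery with one atomizer through 8 consecutive sessions on the existing bench, and report mass per puff by session.
3. Until then, reword Results, Part II and the Discussion to say that concentration per puff is controlled under machine conditions and that home dose is measured by weight, with leaked liquid included in that weight. The Abstract's conclusion needs no change.

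Cost: one added pair of weighings at a visit already planned and supervised, optional bench time on equipment in place, and probably a larger stated spread per puff.

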**Figure 2 figure2:**
[figure not shown]
Aerosol generation tests with our vaping machine. A total of 3 electronic nicotine delivery systems (ENDS) heads were directly screwed onto the vaping machine. Each ENDS head was attached to 2 sampling bottles (impingers) in series by silicon tubes. The impingers were attached to the valve system of the vaping machine and could be set to a specific vaping volume, duration, and frequency through the display at the top left.

#### E-Liquid Formulation and Testing Conditions Optimization

A first series of tests was carried out on the vaping machine to optimize the e-liquid formulation for generating stable aerosol concentrations as well as trapping conditions. We prepared several formulations with different PG/VG ratios (from 0/100 to 50/50), different ethanol amounts (0%-10%), and different DEHP amounts (0.002%-0.3%, w/w) to determine e-liquid formulations that allowed DEHP to be dissolved in the e-liquid and aerosolized by the atomizer. For each ENDS, DEHP-d4 was quantified in the n-hexane of all impingers. The number of impingers (2 and 3), impinger volume (20 and 100 mL), and n-hexane volume in each impinger (13, 50, 75, and 80 mL) were tested for optimal DEHP-d4 trapping conditions.

#### DEHP-d4 Mass Balance and Aerosols Concentrations

We carried out a second series of experiments with the vaping machine to determine mass balance and confirm DEHP-d4 concentration in the aerosols. DEHP-d4 was quantified in the n-hexane of all impingers, in the e-liquid before and after the experiment, and in an acetone/ethanol (50/50 v/v) mixture (acetone, suitable for high-pressure liquid chromatography [HPLC] ≥99.9%, Sigma Aldrich) that was used to extract DEHP-d4 from disassembled ENDS parts at the end of the experiment by the Central Environmental Laboratory of the Ecole Polytechnique Fédérale of Lausanne (EPFL).

#### DEHP-d4 Stability in E-Liquid

The stability of the DEHP-d4 concentration in e-liquid was an important control step for the participants’ safety and to avoid any exposure concentration variability between the participants. The stability test for DEHP-d4 in the e-liquid was performed on the e-liquid stored at room temperature for 1 week and frozen at –20 °C for 2 weeks.

#### Aerosol Particle Mass Distribution in E-Liquid

A portable optical particle counter (aerosol spectrometer, model 1.109, GRIMM) was used to determine the mass distribution of e-liquid particles in the aerosols and assess deposition in the respiratory system [48,49]. Aerosols were generated by equipping the vaping machine with ENDS. The e-liquid used for these tests was composed of a PG/VG ratio of 50/50 with 1% ethanol and was not spiked with DEHP-d4. A total of 6 puffs of aerosol (55 mL×6=330 mL) were diluted in ambient air in a 3 L sampling bag (Tedlar sampling bag, Nutech Instruments Inc). The dilution in ambient air simulated the aerosol dilution in inhaled air by an individual puffing, assuming a 55 mL puff and a 500 mL tidal volume (330 mL/3000 mL=55 mL/500 mL). The particle size distribution profile was then measured. A control test was performed with ambient air.

